### Data management {19}

All data will be stored on a secure institutional REDCap server in a database custom-built for this study. Validation of data fields will be built into this platform where relevant, as well as the use of “required” fields to minimise missing data. Double data entry will not be possible.

### Confidentiality {27}

The research information will be re-identifiable. All participants will be assigned a study ID. A data re-identification key file will be stored as an encrypted file separate to the file containing the data. This will be a password-protected file stored on the hospital server. Only the research team can match the participant’s name to their code number, if it is necessary to do so. The Principal Investigator will be responsible for the secure storage of the data collected in this project. Any hard copy data will be identified by a study ID number only and kept secure in a locked filing cabinet within a locked office. Only named researchers will have access to all data collected in this project. Electronic datasets will be stored securely within the institutional server as a password-protected excel file/on the institutional REDCap platform.

### Plans for collection, laboratory evaluation and storage of biological specimens for genetic or molecular analysis in this trial/future use {33}

No biological specimens will be collected as part of this study.

## Statistical methods

### Statistical methods for primary and secondary outcomes {20a}

Side-to-side difference in anterior tibial translation (the primary outcome), overall ACL-RSI, EQ5D-5L, Marx activity scales, IKDC and KOOS-QOL will be calculated as means, with measures of dispersion reported as standard deviation. Differences between groups will be reported as mean differences, with dispersion reported with confidence intervals. Data normality will be assessed with the Shapiro-Wilk test for continuous parametric assessment. Between-group comparisons, such as the primary outcome of mean difference in GNRB anteroposterior laxity at 2 years, will be assessed with independent samples *t*-tests. If data is found to be non-parametric in distribution, the Wilcoxon rank sum test will be utilised. Comparison of two dichotomous variables, such as return to sport rates and complication rates, will be performed with Fischer’s exact test. Repeated measures such as GNRB measures and mean PROMs will be assessed using mixed effects linear analysis. All tests are two-sided. A *p* value of <0.05 will be considered the cut-off for statistical significance.

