## Introduction

### Background and rationale {6a}

The anterior cruciate ligament (ACL) acts as the primary static constraint to anterior translation and internal rotation of the tibia [1]. ACL rupture is a common knee injury, affecting 0.03–3.67% of athletes annually [2], and most frequently the result of non-contact pivoting sporting injury [2]. ACL rupture in a young person has been established to result in significant loss of participation in sport, the need for reconstructive surgery and prolonged rehabilitation [3], whilst long-term osteoarthritis risk can be increased [3, 4]. Historically, reconstruction with autograft has been the most common pathway to return to sport [5]. Recent reports suggest, however, that return to sport rates are as low as 55% [6], whilst only 40% make a complete functional recovery [7]. Secondary to this, graft failure remains a significant problem, particularly in at-risk populations such as younger and female athletes [8, 9] and those who yield smaller autograft widths [9] at surgical reconstruction. Given these current limitations of ACL reconstruction, Nagelli and Hewett have suggested that return to sport should be delayed to up to 2 years postoperatively [10]. Successful restoration of anterior tibial translatory stability with ACL reconstruction is dependent on the capacity of the ACL graft to withstand appropriate loads during rehabilitation, and the return to the sporting period. As such, synthetic augmentation of native autograft or indeed wholesale replacement of autograft has been of interest for many years. Primarily, these augments were the Ligament Augmentation and Reconstruction System (LARS) prosthesis, the Kennedy Ligament Augmentation Device (LAD), the Leeds-Keio device, the Dacron device and GORE-TEX devices and have been primarily utilised as complete substitutes for autograft [11], with their use as graft augments also reported [12, 13]. However, failure rates are up to 33%, particularly in earlier devices, whilst more recent devices such as the LARS ligament have been reported to be associated with higher rates of persistent effusion and foreign body synovitis [14].

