### Secondary objectives

The secondary objectives are to compare PROMs, complication rates, return to sport rates and examination findings between SA and ST ACLR. The PROMs assessed will include the Marx activity scale, ACL RSI, IKDC, the KOOS QOL and the EQ5D-5L scale. Complications assessed will include post-operative pain levels, graft failure rates, contralateral knee ACL rupture, return to theatre and findings including rates of particulate-related synovitis, sterile effusion, persistent effusion and symptomatic arthrofibrosis of the knee. Return to sport data will include rates of return to sport, timing of return to sport and rates of return to the previous level of the sport. Examination findings assessed will include the presence of effusion, knee range of motion and the presence and grade of the Lachman test, anterior drawer and pivot shift tests.

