#### Secondary outcomes

Secondary outcomes are fourfold and will include (i) PROMs, (ii) return to sport rates, (iii) complications and (iv) examination findings.i)PROMs will be recorded preoperatively and post-operatively at 6 weeks, 3 months, 12 months and 24 months. PROMs collected will include the following:EQ5D-5L: The EuroQol EQ-5D-5L is a validated, generic, self-reported outcome measure covering five health domains that are used to facilitate the calculation of quality-adjusted life years (QALYs) in health economic evaluations. The original EQ-5D questionnaire contained three response options within each of five health domains (mobility, self-care, usual activities, pain/discomfort and anxiety/depression) [33]. More recently, the EQ-5D-5 L has been developed to overcome problems with ceiling effects and to improve sensitivity [43]. The 5 L version consists of the same five domains as the original but with five response options.The International Knee Documentation Committee (IKDC) score: The IKDC is a knee-specific patient outcome questionnaire often used after ACL reconstruction [31]. It is a subjective tool that provides an overall patient score (0–100), often interpreted as a measure of function, where higher scores represent a greater function. It aims to address three categories: symptoms, activity and overall function, and has shown adequate test-retest reliability and good construct validity in patients with issues at the knee [44].Knee injury and Osteoarthritis Outcome Score Quality of Life sub-scale (KOOS-QOL): This subscale is a 4-item questionnaire designed to evaluate the knee-specific quality of life, has been utilised among ACL surgical trials [30] and has been established to have validity, responsiveness and reliability in patients undergoing ACLR [45].ACL return to sport index (ACL-RSI): Psychological readiness to return to sport will be evaluated with the ACL-RSI. It is a 12-point questionnaire validated to evaluate a patient’s confidence and readiness to return to sport [34] and exhibits high internal validity and structural consistency [46]. Given the theoretical increased stability offered by suture tape augmentation, particularly in the early rehabilitative period, it follows that patients treated with this may experience improved perception of knee function and subsequent confidence in rehabilitation and sporting activity across the early postoperative period.Self-reported pain: We will record postoperative pain levels and long-term knee pain scores utilising 10-point visual analogue scale pain scores (VAS) where 0 is no pain and 10 is the worst pain imaginable.ii)Complications:We will record complications and adverse events including wound complications, infection rates, return to surgery, e.g. meniscal tears, graft failure, contralateral knee ACL rupture, residual effusion, rates of symptomatic arthrofibrosis of the knee and second look arthroscopy findings and the rates of sterile effusion. These will be recorded upon review of each patient’s medical record at 2 years.iii)Return to sport and activity:Return to sport and activity will be assessed via a self-reported questionnaire delivered concomitantly with PROMs preoperatively and post-operatively at 6 weeks, 3 months, 12 months and 24 months. Return to activity will be evaluated through the Marx activity scale, a four-item activity rating scale which has been shown to have excellent retest reliability in patients with knee injuries [32]. Participants will be asked to record on a scale of 0–4 how often they are able to perform each of running, cutting, deceleration and pivoting in their most active state across the preceding 12 months. A maximum score is 16 points. Participants will also be asked about their dichotomous return to sport status, their expectations regarding timing of return to sport, return to preinjury level of sport and the time postoperatively to return to sporting activity. These questions, along with the full set of pre-operative and post-operative PROMS, are included in Additional file 1.iv)Examination findingsExamination findings will be taken preoperatively at examination under anaesthesia and post-operatively at 6 weeks, 3 months and 12 months. Examination findings including the range of motion (ROM), the presence of knee effusion, Lachmans, pivot shift and anterior drawer testing will be recorded. All assessments will be undertaken by lead surgeons S.T, L.B.

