### Methods in analysis to handle protocol non-adherence and any statistical methods to handle missing data {20c}

All principal analyses will be based on the intention-to-treat principle, analysing participants in the groups to which they are randomised. Missing data will be quantified and if possible multiple imputation will be used; otherwise, simple imputation will be used. Owing to the nature of enrolment and randomisation in this study, it is unlikely that a participant will be randomised and subsequently not receive the intervention, and thus adherence does not apply directly to the intervention arm.

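### Timing of return to sport is a declared comparison, but the only rule that reaches it (t-test or Wilcoxon) needs a return time that non-returners do not have

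*Protocol article*

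**What the plan says.** Under Secondary objectives, the protocol article sets out what is compared between arms for sport: "rates of return to sport, timing of return to sport and rates of return to the previous level of the sport". Timing therefore stands as an item of its own beside the rates.

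Under Secondary outcomes, participants are asked for their yes/no return status and, among other items, "return to preinjury level of sport and the time postoperatively to return to sporting activity". The questionnaire is "delivered concomitantly with PROMs preoperatively and post-operatively at 6 weeks, 3 months, 12 months and 24 months".

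Section {20a} covers primary and secondary outcomes. Its general rule is: "Between-group comparisons, such as the primary outcome of mean difference in GNRB anteroposterior laxity at 2 years, will be assessed with independent samples" t-tests. The fallback is: "If data is found to be non-parametric in distribution, the Wilcoxon rank sum test will be utilised". Fisher's exact test is assigned to dichotomous variables, with return to sport rates as a named example, and a linear mixed model is assigned to repeated measures. Timing of return is not named. The article gives no time-to-event method and no censoring rule.

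Section {20c} adopts intention to treat for the principal analyses and adds: "Missing data will be quantified and if possible multiple imputation will be used; otherwise, simple imputation will be used". Section {18b} ends data collection at withdrawal or graft failure.

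**The concern.** Time to return exists only for a patient who returns. For anyone else the record is either not returned by 24 months or not returned when last seen. Neither is a number that a t-test can use.

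Of the rules in {20a}, Fisher's test needs a dichotomy and the mixed model needs repeated scores, so only the t-test/Wilcoxon rule can reach a single return time. Its most natural use is on the patients who have one. Whether a patient returns may itself depend on the treatment, so the two sets of returners are not the randomised groups.

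Two things are at stake. The first is power, because each non-return by 24 months is informative and would be set aside. The second is direction. If tape brings back some patients who would otherwise not have returned, and they return late, they raise the tape arm's mean, and a benefit can read as a delay.

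**Working it through.** **Inputs from the protocol.** 66 randomised, 1:1; 30% expected dropout (Sample size); follow-up to 24 months (Trial design); graduated return from 6 to 9 months ({11d}); two-sided 0.05 ({20a}); and a background statement that "return to sport rates are as low as 55" per cent (Background). The plan gives no expected value, SD or power for timing of return, so there is no figure of its own to reproduce here.

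**How many patients have a time.** 66 × 0.70 = 46.2, or about 23 per arm. At 55% return, 46.2 × 0.55 = 25.4 patients have a return time and 45% have none. The 55% is a lower background figure, so 45% is near the upper end.

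**Direction, closed form.** Assumed: in the standard arm 55% return at a mean of 10 months. In the tape arm the same 55% return 0.5 month sooner, and a further share *e* returns at time *L*.
- Returners-only mean, tape = (0.55 × 9.5 + *e* × *L*) / (0.55 + *e*).
- Restricted mean to 24 months, tape = 0.55 × 9.5 + *e* × *L* + (0.45 − *e*) × 24.
- Standard arm: 10.0 among returners; restricted mean 0.55 × 10 + 0.45 × 24 = 16.3.

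For *e* = 0.20 and *L* = 18, the returners-only mean is (5.225 + 3.6) / 0.75 = 11.77, and the restricted mean is 5.225 + 3.6 + 6.0 = 14.8.

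| Extra returners in tape arm | Returners-only difference (months) | Restricted-mean difference (months) | Reversed? |
|---|---|---|---|
| +20 points at 18 months | +1.8 | −1.5 | yes |
| +10 points at 18 months | +0.8 | −0.9 | yes |
| +20 points at 14 months | +0.7 | −2.3 | yes |
| +20 points at 11 months | −0.1 | −2.9 | no |
| none | −0.5 | −0.3 | no |

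The first row was simulated with a within-group SD of 2 months (assumed; 4,000 runs). The returners-only t-test was significant in the wrong direction in 21% of runs with 24 per arm and 32% with 33 per arm. Wilcoxon among returners did so in 10% and 13%, so the fallback reduces the problem but does not remove it.

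**Power, proportional effect.** Assumed: return time = 6 months + exponential, with the rate set to give the stated return by 24 months; 23 per arm; 4,000 runs. For 55% against 80% the hazard ratio is ln(0.20)/ln(0.45) = 2.0. Fisher power is exact: the sum of binomial probabilities over all tables with p < 0.05.

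| Return, standard vs tape | t-test, returners only | Log-rank, all patients | Fisher on rates | Mean difference among returners (months) |
|---|---|---|---|---|
| 55 vs 55% | 4.7% | 5.1% | – | – |
| 55 vs 70% | 6.4% | 19.2% | 11% | −0.57 |
| 55 vs 80% | 8.9% | 49.1% | 33% | −1.09 |
| 55 vs 90% | 21.4% | 87.3% | 70% | −2.00 |

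Repeat runs agreed to within simulation error; for 55 vs 80% the t-test lies at 9 to 10%. Here the returners-only difference has the right sign; the loss is in power.

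**Late extra returners in the same model.** If the extra returners are spread evenly over 12 to 24 months and nobody returns later than otherwise, the returners-only mean is about 0.9 months later with tape at 55 vs 70% and about 1.3 months later at 55 vs 80%. The sign is wrong in roughly 68% and 76% of runs. In this scenario the log-rank test has little power advantage over Fisher's test. What it protects is the direction of the timing result.

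**The case against.** The strongest reply is that the plan never commits the error. Section {20a} does not list timing among the outcomes summarised as means, and the t-test sentence names only laxity. This is a condensed article, and a separate analysis plan may deal with the point. That stands in part: nothing here shows that the trial will analyse timing wrongly. But {20a} is not silent. It lays down a general rule for between-group comparisons under a heading that covers secondary outcomes, and that rule does not suit one of the declared comparisons.

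A reader might infer more than the text supports:
- **That non-returners will be dropped or given an invented date.** Neither is stated. Return status is collected separately, so non-return at 24 months is a known status and not plainly missing data. A Wilcoxon test could rank non-returners last and keep them. That would not deal with patients whose data stop before 24 months, and the plan makes Wilcoxon a fallback for non-normality only.
- **That the t-test/Wilcoxon rule is the only one for continuous outcomes.** It is not; there is also the mixed model, although it does not suit a single time.
- **That the log-rank gain is all new information.** Much of it is the difference in rates, which Fisher's test already examines. At 55 vs 80% the gain over Fisher is 49% against 33%, not 49% against 9%. The rates would also be reported beside the timing result, so a reversed timing result would not stand alone.

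**Conclusion.** The point holds as a mismatch between a declared secondary comparison and the general rule that would apply to it. Followed as written, the rule would most naturally compare returners only, against the intention-to-treat principle in {20c}.

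Under the assumed exponential times with 23 per arm and 55 vs 80% return, the returners-only t-test has about 10% power and a log-rank test about 49%, while the planned Fisher test on rates has about a third. A wrong direction, of the order of 1 to 2 months, arises when tape adds late returners. It does not arise when the extra returners are early or absent, so reversal is a possibility and not a prediction.

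Only the 55%, the 24-month horizon and the 30% dropout come from the protocol. The time distributions and effect sizes are assumptions. The primary outcome, sample size and randomisation are unaffected. The wording should be corrected, but this is not a critical fault.

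**What to change.** In {20a}, state that timing of return to sport is analysed as time from surgery to return in all randomised patients. Those not returned are censored at their last questionnaire, at 24 months at most. Show Kaplan-Meier curves and compare arms with a log-rank test or Cox model stratified by the age stratum used at randomisation, or by restricted mean time to 24 months. Keep any mean among returners descriptive.

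In {20c}, state that imputation does not apply to the return time of a patient known not to have returned.

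Because data collection stops at graft failure, censoring there may be informative. Treat graft failure before return as a competing event or as non-return, at least in a sensitivity analysis.

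The cost is a few sentences, with no new data, visits or patients. The one drawback is that a hazard ratio or a curve is less direct than a mean difference in months; restricted mean time keeps the result in months if that is preferred.

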## Methods: participants, interventions and outcomes

### Study setting {9}

This study will be conducted across three subsidiary hospitals, within a single major metropolitan Australian academic hospital (site details available on ANZ Trial Registry). All patients will be recruited from the adult orthopaedic outpatient clinic. A total of 66 participants will be recruited and randomised to a treatment arm. Owing to the nature of the randomisation model, greater than 66 patients may be recruited to reach the eventual target randomisation number. All data will be collected within Australia.

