### Sample size {14}

All statistical methods and power analysis were developed through consultation with an independent statistician. Power analysis was performed with G*power 3.1 Software. To achieve a minimum 80% statistical power with an alpha value of 0.05, power analysis based on a hypothesised mean residual side-to-side difference of 2 mm of anteroposterior tibial translation yielded a sample size of *n*=48 (24 per group) utilising an expected independent *t*-test [47–50]. Although previously published KT-1000 data was utilised for power analysis, it has been shown that the GNRB exhibits similar absolute measures in side-to-side anterior tibial translation to KT-1000 utilised by experienced observers, whilst having reduced scatter around the mean [38]. This would mean that utilising KT-1000 published data to establish a power analysis would be a conservative method, and likely over-estimate the required sample size to detect significant differences.

Secondary power analysis based on 2-year IKDC total scores yielded a total sample size of 48 (*n*=24 in each group) to detect significant differences with 80% power and an alpha value of 0.05 with an anticipated independent sample two-tailed *t*-test. This is based on a previous retrospective study of suture-tape ACL reconstruction which reported a mean change from baseline IKDC of 56 ± 17 in SA-augmented ACLR, compared with 38 ± 25 in conventional ACLR [29, 51]. Secondly, previous studies evaluating the IKDC [51] which reported that a change score of 12.8 points would be sufficient to detect differences between those who have and have not had improved knee outcomes. Power analysis yielded a sample size of 48. Dropout rates are expected to be 30% based on institutional experience, owing to loss to follow-up and contralateral ACL rupture and graft failure, and as such 66 patients will be recruited. This is expected to take approximately 1–2 years of recruitment based on historical institutional caseloads.

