## Assignment of interventions: allocation

### Sequence generation {16a}

The randomisation design is a computer-generated permuted single-blind block randomisation. The randomisation sequence will be developed by an independent statistician, with all other research team members blinded to the randomisation sequence. Participants will be randomised using permuted block randomisation which allows for a better guarantee of equal-sized treatment groups [52] whilst protecting against prediction of allocation towards the end of the recruitment period. Randomisation will be allocated in a 1:1 fashion, whereby patients will undergo either standard ACLR or suture tape-augmented ACLR. Randomisation will be stratified according to age greater than 25 years.

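### Fisher's exact test for return to sport is valid but conservative at this size (true error about 3 to 4%); Boschloo's exact test would recover roughly 2 to 10 points of power

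*Protocol article*

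**What the plan says.** The section on statistical methods {20a} states that comparison of dichotomous variables, "such as return to sport rates and complication rates, will be performed with Fischer’s exact test". It adds that "All tests are two-sided" and that a p "value of <0.05 will be considered the cut-off for statistical significance".

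Return to sport is a secondary outcome. The protocol gives it no planning rate, target difference or power. The only rate appears in the background {6a}, where recent reports are said to suggest "that return to sport rates are as low as 55" per cent.

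On numbers, {9} says "A total of 66 participants will be recruited and randomised to a treatment arm", and {16a} says "Randomisation will be allocated in a 1:1 fashion". The sample size section {14} rests on laxity and IKDC and arrives at 24 "in each group) to detect significant differences with 80% power and an alpha value of 0.05". It also says "Dropout rates are expected to be 30% based on institutional experience". Section {20c} plans multiple imputation where possible.

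**The concern.** In a 1:1 randomised trial the arm sizes are set by design, but the total number of patients who return to sport is not. Fisher's test conditions on that total as well. With a few dozen patients per arm, few p-values are then attainable, and the largest attainable error below 5% is often well below it. The unused part of the 5% is lost power.

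Boschloo's test takes the Fisher p-value as its statistic. It sets the cut-off so that the error rate, maximised over the unknown common rate, does not exceed 5%. It therefore rejects whenever Fisher's test does, and for some further tables too.

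At stake is some power on a secondary efficacy comparison that is already thin, and low return-to-sport rates are part of the trial's rationale. The primary outcome and the sample size are unaffected.

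**Working it through.** **Inputs from the protocol.** Two-sided test at 0.05 {20a}; 66 randomised 1:1, so 33 per arm if balanced {9, 16a}; 24 per arm as the required number and 30% dropout {14}. After dropout, 66 × 0.70 = 46.2, about 23 per arm. The number analysed could thus lie anywhere from about 46 to 66.

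**Assumptions.** A control return rate of 55% (background figure, not a planning rate) and a rate with tape of 70 to 95%. The protocol states neither as a design value.

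**The plan's own figure.** The protocol gives no figure for return to sport. Its 24 per group for IKDC does reproduce: pooled SD = √((17² + 25²)/2) = √457 = 21.38; d = (56 − 38)/21.38 = 0.842; the two-sample t-test needs 23.1, so 24 per group, with power 81.5%. Hence 24 per arm is a fair base case.

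**Method.** For arm sizes n₁ and n₂, list every table (x₁, x₂). The probability of rejection at true rates p₁ and p₂ is

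Σ Bin(x₁; n₁, p₁) × Bin(x₂; n₂, p₂) × 1[test rejects].

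Fisher rejects if its two-sided p < 0.05. Boschloo rejects if the same p ≤ c, where c is the largest value that keeps the maximum error over all common rates at or below 0.05. At 24/24, c is about 0.080; at 33/33, about 0.077; at 23/24, about 0.060.

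**True error at a common rate of 55%.**
- 24/24: Fisher 2.9%, Boschloo 4.7%
- 33/33: Fisher 3.5%, Boschloo 4.2%
- 23/23: Fisher 2.6%
- 24/22, 25/23, 23/24 and 32/34: Fisher 3.8 to 4.0%
- Averaged over random 30% dropout from 33 per arm: Fisher 3.4%

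Boschloo's maximum error over all rates stays at or below 5% in every case.

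**Power with Fisher, and gain with Boschloo in points, against 55%** (unequal arms averaged over which arm is larger):

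| Arms | vs 75% | vs 80% | vs 85% |
|---|---|---|---|
| 24/24 | 21.9%, +8.0 | 35.6%, +9.0 | 53.4%, +8.1 |
| 33/33 | 31.4%, +8.2 | 48.9%, +9.7 | 68.6%, +8.4 |
| 24/22 | 23.8%, +4.7 | 37.3%, +6.5 | 54.6%, +7.0 |
| 25/23 | 25.7%, +4.1 | 39.9%, +6.1 | 57.4%, +6.8 |
| 23/24 | 25.5%, +2.3 | 39.9%, +3.3 | 57.8%, +3.4 |
| 32/34 | 36.0%, +3.3 | 54.6%, +4.4 | 73.9%, +4.1 |
| Random 30% dropout | 23.8%, +4.6 | 37.5%, +5.8 | 54.6%, +6.0 |

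Under random 30% dropout the two completer arms are equal in only about 11% of trials, so the first two rows are the favourable case. Outside these rates the gain at 24/24 is smaller: +5.9 (vs 70%), +5.5 (vs 90%) and +2.4 (vs 95%).

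**Complications.** At a common rate of 5%, Fisher's true error at 24/24 is 0.4%. For an assumed 5% against 20%, power goes from 23.7% to 24.9% at 24/24 and from 29.3% to 38.3% at 33/33.

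**Which two-sided version.** Some software doubles the smaller one-sided Boschloo p-value. With equal arms of 24 this gives the same power as above. With unequal arms it no longer rejects whenever two-sided Fisher does: at 24/22, two tables that Fisher rejects are lost. For 55% (arm of 24) against 80% (arm of 22), Fisher's power of 38.2% rises to only 41.0%; the version enumerated above gains 6.2 points there. At 23/24 the doubled version gains nothing for this contrast.

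**The case against.** The strongest reply is that nothing in {20a} is wrong. Fisher's test keeps the error at or below 0.05 whatever the true rate, and the protocol nowhere says that the attained error equals 5%. A discrete test commonly falls short of its level, and Boschloo's does too (4.2% at 33/33). Choosing between two valid exact tests is then a matter of efficiency. This stands. A reader might infer that the trial is not using its stated level; the protocol does not support that.

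A reader might also take 8 to 10 points as the general loss. That needs exactly equal analysed arms and a difference of 20 to 30 points from 55%, and with 30% dropout equality is unlikely. Nor is 55% the trial's planning rate: it is a low value cited from the literature.

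Two further points stand. Neither exact test combines directly with the multiple imputation in {20c}, so the 33/33 figures apply only if nearly everyone is observed. Both tests also ignore the stratification of randomisation by age. Finally, the change does not rescue the comparison: for 55% against 80%, power after it is still only about 45% at 24/24 and 59% at 33/33.

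What the reply does not remove is that {20a} fixes a test that another exact test with the same 5% guarantee can match or better at every true rate.

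**Conclusion.** The point holds as an optional improvement. Fisher's test runs at about 3 to 4% true error at 23 to 34 per arm, with a common rate of 55% assumed. Boschloo's test, ordered by the two-sided Fisher p-value, keeps the 5% limit and cannot lose power.

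For return to sport the gain is roughly 2 to 10 points across 55% against 75 to 85%: 8 to 10 with exactly equal arms, mostly 3 to 7 with arms one or two apart (2.3 in the least favourable cell), and about 5 to 6 on average under 30% dropout. It shrinks outside those rates and can be close to zero for rare complications. All power figures rest on assumed rates, because the protocol gives none for this outcome.

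**What to change.** In the statistical methods section {20a}, replace Fisher's exact test for dichotomous outcomes with Boschloo's exact unconditional test applied to observed data. State that the two-sided Fisher p-value is the test statistic, since the guarantee of never losing power depends on that version. Make the change before any outcome comparison by arm.

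The cost is about one sentence and a check that the chosen software implements that version. No patients are added. The one small downside is that, as with Fisher's test, any imputed analysis of a binary outcome needs a separate model-based or risk-difference estimate, and the plan should say so.
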